#### Data analysis

Prior to hypothesis testing, the demographics and patients’ characteristics will be compared between TRE vs. control groups and the relevant variables (e.g., age) that differ by group will be included as confounders in hypotheses testing. To provide estimates of efficacy comparing TRE vs. an unrestricted eating pattern to alleviate fatigue, the first objective is to longitudinally evaluate the between-arm difference in mean change in MFSI score from baseline to post-intervention (12 weeks after baseline) in a linear mixed model. A data collection point at 6 weeks is also included in order to capture any effects of the intervention at a shorter time point. The outcome will be MFSI score and the fixed effects will include arm (TRE vs. control), time (baseline, 6, and 12 weeks), and interactions between arm and time. Statistical significance of the arm×time interaction will be assessed at an alpha of 0.05. Participants will be included as a random effect accommodating the correlations between repeated measures. If any aforementioned potential confounders (e.g., age, body mass index, psychological symptoms, time since completion of treatment) are not evenly distributed between the two groups, they will be added to the model. The results of the analyses together with the estimates of distribution parameters (e.g., mean, SD) of MFSI values as well as the change scores will be used in planning future randomized trials. In addition to statistical significance, we will assess the effect sizes and whether any changes seen are clinically meaningful. The MFSI has a published MCID of 4.5 points [49].

A second objective is to assess the sustainability of TRE three months after the intervention. At 24 weeks, follow-up will occur with several questionnaires. Participants will be asked to self-report the time of their typical first food/beverage intake and their typical last food/beverage intake at night over the previous week. The eating window will be calculated, and its length will be compared between arms using a t-test. We will also evaluate the proportion of patients adhering to 10-h window. We hypothesize those in the intervention group will have adopted a significantly shorter eating window than those in the control group.

Mechanistic objectives are to assess intervention effects on rest-activity rhythms and glucose parameters. Similar models as for our primary objective will be constructed with appropriate dependent variables. The statistical results will be adjusted for multiple testing using the Benjamini-Hochberg method [71] at a q = 0.15 level.

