### Statistical analysis

#### Sample size and power calculation

The protocol is approved to recruit 96 participants. They will be randomized in a 1:1 ratio, intervention: control (48:48) using computer-generated block randomization with blocks of 2 or 4. The estimated attrition is approximately 20%, thus the estimated retention rate is 76 (38:38) evaluable participants. This sample size is appropriate for phase II randomized studies and it will allow us to obtain preliminary estimates of descriptive statistics [mean, standard deviation (SD), confidence intervals (CI), and correlations between repeated measures] [68]. The primary endpoint is the change in fatigue as measured by the MFSI [39] from baseline (T1) to 12 weeks (T3), with a midpoint assessment at 6 weeks (T2). The sample size calculation was based on repeated measure analysis of variance (ANOVA). Assuming correlations [69] of 0.60 between repeated MFSI measurements, a total sample size of *n* = 76 will provide 80% power at the 0.05 two-sided significance level to detect a medium effect size (difference in change between groups divided by the baseline SD of the MFSI score) of 0.50 for the intervention effect. The estimate of effect size is based on our feasibility trial and studies with similar interventions. Our feasibility trial [18] yielded an effect size of 0.55 (within-subject, pre- to post-intervention change) using the Functional Assessment of Chronic Illness Therapy-Fatigue (FACIT-F) questionnaire [70], fatigue subscale, which is likely an overestimate of between-group differences. We decided to employ the MFSI instead of the FACIT-F for this study because the MFSI captures multidimensional aspects of fatigue; the FACIT-F captures multidimensional aspects of quality of life including fatigue, therefore the MFSI is a more appropriate construct for a primary outcome of fatigue.

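### The primary significance rule is the arm×time interaction over three visits; if time is categorical, it does not specifically test the week-12 endpoint

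*Protocol article*

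**What the plan says.** The protocol article, Sample size and power calculation, fixes the endpoint: "The primary endpoint is the change in fatigue as measured by the MFSI [39] from baseline (T1) to 12 weeks (T3"), and describes week 6 as a midpoint. Data analysis repeats it as the first objective, which is to "evaluate the between-arm difference in mean change in MFSI score from baseline to post-intervention (12 weeks after baseline) in a linear mixed model".

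The model follows in the same paragraph: the "fixed effects will include arm (TRE vs. control), time (baseline, 6, and 12 weeks), and interactions between arm and time", and "Participants will be included as a random effect accommodating the correlations between repeated measures". The reason given for week 6 is: "A data collection point at 6 weeks is also included in order to capture any effects of the intervention at a shorter time point".

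The one significance rule stated for this model is: "Statistical significance of the arm×time interaction will be assessed at an alpha of 0.05". No week-12 contrast is named as the test. The article does not say outright whether time is categorical or continuous.

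The power statement rests on a repeated-measures ANOVA with an unnamed contrast. It says that 76 evaluable participants "will provide 80% power at the 0.05 two-sided significance level" for an effect of 0.50 baseline SD at a correlation of 0.60.

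**The concern.** The endpoint is one number: the arm difference in change at week 12. The rule for significance covers every way in which the two arms' profiles over three visits can differ. With time as a three-level factor, the interaction has (2−1)×(3−1) = 2 degrees of freedom and favours neither visit. A difference at week 6 that has gone by week 12 counts towards significance just as a week-12 difference does, and the plan itself includes week 6 in order to look for earlier effects.

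Two things are at stake. A significant primary test need not say anything about week 12. And the power to detect a week-12 effect becomes dependent on what happens at week 6. The results are meant to inform a phase III trial, and the mechanistic outcomes are to be analysed with similar models, so the ambiguity carries over to them.

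**Working it through.** **Inputs, all from Sample size and power calculation:** n = 38 per arm (76 evaluable); effect δ = 0.50 baseline SD; correlation ρ = 0.60; two-sided α = 0.05. **Assumptions:** baseline SD = 1 at every visit, equal correlations (as a random intercept implies), complete data for the 76, categorical time.

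**1. The plan's own 80%.** Power = Φ(δ / (SD·√(2/n)) − 1.96), with √(2/38) = 0.2294.

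| Contrast | Variance | SD | Power at 38 per arm |
|---|---|---|---|
| Mean of weeks 6 and 12, minus baseline | (1+0.6)/2 + 1 − 2(0.6) = 0.60 | 0.775 | 80.3% |
| Week 12 minus baseline | 2(1−0.6) = 0.80 | 0.894 | 68.3% |
| Week 12 adjusted for baseline | 1 − 0.6² = 0.64 | 0.80 | 77.8% |

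For the endpoint as written: 0.50/(0.894 × 0.2294) = 2.437; 2.437 − 1.96 = 0.477; Φ(0.477) = 68.3%. With t distributions it is 67.2% (two-sample t) or 67.8% (pooled mixed-model residual). The baseline-adjusted figure becomes 76.7%. Of the two-sided contrasts tried, only the average of weeks 6 and 12 minus baseline gives the stated 80%. That is neither the week-12 change nor the 2-df interaction.

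**2. Rejection rate of the 2-df interaction.** Let g be the vector of true arm differences at baseline, week 6 and week 12, and ḡ its mean. The noncentrality is λ = (n/2)·Σ(g − ḡ)²/(1 − ρ) = 19·Σ(g − ḡ)²/0.4, referred to F with 2 and 2×(76−2) = 148 df.

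| True differences (SD) | Σ(g − ḡ)² | λ | 2-df interaction | Week-12 change contrast |
|---|---|---|---|---|
| 0, 0.50, 0 | 0.1667 | 7.917 | 70.3% | 5% |
| 0, 0.40, 0 | 0.1067 | 5.067 | 50.1% | 5% |
| 0, 0.30, 0 | 0.0600 | 2.850 | 30.2% | 5% |
| 0, 0.25, 0.50 | 0.1250 | 5.937 | 57.0% | 67.8% |
| 0, 0.50, 0.50 | 0.1667 | 7.917 | 70.3% | 67.8% |

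**3. Check by simulation, 20,000 trials per profile.**
- Profile (0, 0.50, 0): the interaction was significant in 70.6%, and significant without a significant week-12 contrast in 65.6%.
- Profile (0, 0.25, 0.50): interaction 56.7%, week-12 contrast 67.6%. In 12.6% of trials the week-12 contrast was significant and the interaction was not.
- No effect at any visit: interaction 5.2%, so the level holds. About half of those rejections (49%) came without a significant week-12 contrast.

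**4. If time were linear.** With visits at 0, 6 and 12 weeks and complete data, the slope contrast has weights −1, 0, 1. The interaction would then have 1 df and match the week-12-minus-baseline contrast, and a week-6-only effect would contribute nothing to it.

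**The case against.** The article never calls the interaction an omnibus or 2-df test, and under linear time the mismatch disappears (step 4). That caveat stands. Against it, the article lists three discrete occasions and refers to interactions in the plural, so categorical time is the more natural reading. If linear time was meant, a sentence is still needed to say so.

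The objective sentence in the same paragraph already names the "between-arm difference in mean change in MFSI score from baseline to post-intervention (12 weeks after baseline) in a linear mixed model", and an article may leave the exact contrast to an analysis plan. The intended quantity is indeed clear. But the article does more than stay silent: it states a decision rule, and that rule is not a test of the quantity.

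A reader might infer that the trial would declare its primary objective met with a zero effect at week 12. The article does not say this. No sentence makes a significant interaction sufficient for success, the aim is initial estimates of efficacy, and effect sizes and the 4.5-point MCID are to be considered as well. A reader might also infer inflated type I error or a general loss of power. Neither follows: the level holds when there is no effect at any visit, and for an effect sustained from week 6 the interaction does slightly better than the unadjusted change contrast.

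The 70% figure needs the full design effect at week 6 and none at week 12, while participants are still on the intervention. Nothing in the article predicts that profile, which is why the smaller effects are shown beside it.

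**Conclusion.** The point holds as a mismatch between endpoint and test, conditional on categorical time. The stated rule keeps its overall 5% level, but a significant result cannot be attributed to week 12, the visit that defines the endpoint. At the plan's own inputs, a week-6-only effect of 0.50, 0.40 or 0.30 SD gives significance about 70%, 50% or 30% of the time, against 5% for the week-12 contrast.

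The consequence for power depends on the profile. For 0.50 SD at week 12, the interaction has 57% against about 67–68% under linear build-up, and 70% against about 68% when the effect is sustained. None of the profiles examined gives the interaction the stated 80%, and neither does the week-12 change contrast.

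The figures assume equal variances and correlations and complete data for 38 per arm.

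**What to change.** In Data analysis, replace the sentence on the interaction with:

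> The primary test is the single-df between-arm difference in change from baseline to week 12, estimated as the week-12 contrast from the mixed model with categorical time, two-sided alpha 0.05, with 95% CI; the week-6 contrast and overall arm×time test are secondary.

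In Sample size and power calculation, name the same contrast and restate its power at 38 per arm for 0.50 SD: about 67–68% as an unadjusted change, or about 77% if the week-12 contrast is adjusted for baseline. If adjustment is chosen, the replacement sentence must say so. State which contrast is primary for the mechanistic models too, since they follow this one.

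Data collection does not change, and recruitment is expected to run through 2027 with primary results in 2028, so the edit can precede analysis. The cost is a less favourable stated power. For scale, 80% would need 51 per arm unadjusted (102 evaluable; 102/0.8 = 127.5, so 128 randomised) or 41 per arm adjusted (82 evaluable; 82/0.8 = 102.5, so 103 randomised), against the 96 planned. For a phase II trial aimed at initial estimates, reporting the lower power openly is a reasonable alternative to enlarging it.

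### The primary model gives each arm its own baseline mean, so at the protocol's correlation of 0.60 the week-12 contrast has 25% more variance than it needs; this costs precision and causes no bias

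*Protocol article*

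**What the plan says.** The Data analysis section sets the first objective as the between-arm difference in mean MFSI change from baseline to 12 weeks, estimated in a linear mixed model. On the fixed part it says: "The outcome will be MFSI score and the fixed effects will include arm (TRE vs. control), time (baseline, 6, and 12 weeks"), together with the arm×time interactions. On the covariance it says: "Participants will be included as a random effect accommodating the correlations between repeated measures". The significance test named is the arm×time interaction at 0.05, which has 2 degrees of freedom with three time levels. Covariates enter only if they turn out to be unevenly distributed between the arms, and baseline MFSI is not among the examples listed. The mechanistic outcomes are to use similar models.

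The Procedures section places randomisation after the baseline assessments.

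The Sample size and power calculation section gives the planning values. "Assuming correlations [69] of 0.60 between repeated MFSI measurements", it claims that "a total sample size of *n* = 76 will provide 80% power" for an effect of 0.50, defined as "difference in change between groups divided by the baseline SD of the MFSI score".

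**The concern.** Because participants are randomised after baseline is measured, any baseline difference between the arms is chance. A model that estimates a separate baseline mean in each arm ignores this. It subtracts the whole observed baseline difference from the week-12 difference, when only the part predicted by the correlation should be removed. The stated objective is the baseline-to-week-12 contrast. Its estimate is to be set against a 4.5-point minimal clinically important difference and used to plan later trials, so its precision matters.

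The covariance raises a second question. The natural reading of a participant random effect is a random intercept, which makes all pairs of visits equally correlated. If scores 12 weeks apart correlate less than scores 6 weeks apart, the pooled residual variance understates the standard error of the week-12 contrast.

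**Working it through.** **Inputs.** From the sample size section: 38 evaluable per arm, effect d = 0.50 baseline SD, correlation r = 0.60, two-sided alpha 0.05. From Data analysis: arm, three-level time, arm×time and a participant random effect. Baseline SD is set to 1, with equal variances and complete data. Power is for two groups with variance factor V and standard error √(2V/38).

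**The plan's own figure.** The stated 80% is reproduced if the contrast is the mean of weeks 6 and 12 minus baseline: V = 1 + (1 + 0.60)/2 − 2(0.60) = 0.60. This gives power 80.3% by normal approximation (79.3% by t) and a total of 76. It does not reproduce for the week-12 change.

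**Week-12 contrast.**

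| Model | V | Power at 38 per arm (t) | Total N for 80% (normal) |
|---|---|---|---|
| Free baseline means (as written) | 2(1 − 0.60) = 0.80 | 67.2% | 102 |
| Common baseline mean, or baseline covariate | 1 − 0.60² = 0.64 | 76.7% | 82 |

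Variance ratios: 0.64/0.80 = 0.80, so 20% lower; 0.80/0.64 = 1.25, so equal to 25% more participants.

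In general the saving is 1 − (1 − r²)/[2(1 − r)] = (1 − r)/2. It is 30% at r = 0.4, 25% at 0.5, 20% at 0.6 and 15% at 0.7.

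**The named 2-df test.** The noncentrality with free baseline means is (38/2) × Σ(dⱼ − d̄)²/(1 − r). With a common baseline it is (38/2) × d′S⁻¹d, where d holds the week-6 and week-12 effects and S has 1 − r² = 0.64 on the diagonal and r − r² = 0.24 off it.
- Effects 0.25 at week 6 and 0.50 at week 12: noncentrality 5.94 against 7.56; power 57% against 68%.
- Effects 0.50 at both visits: 7.92 against 10.80; power 70% against 84%.

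**Conditional check of the standard error.** Under a random intercept the squared standard error of the week-12 contrast is proportional to 2(1 − mean r). The true value is proportional to 2(1 − r₁₃), where r₁₃ is the baseline-to-week-12 correlation. Apart from the 0.60 row, the correlations below are assumptions; the protocol gives none that fall with time. Type I error comes from simulations of 20,000 null trials with 38 per arm; a range covers repeated runs.

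| r₁₂ / r₂₃ / r₁₃ | Model SE / true SE (formula) | Type I error, 1-df week-12 contrast | Type I error, 2-df arm×time test |
|---|---|---|---|
| 0.60 / 0.60 / 0.60 | 1.00 | 4.9–5.0% | 4.9–5.0% |
| 0.70 / 0.70 / 0.60 | √(0.667/0.80) = 0.91 | 7.2% | 5.1% |
| 0.65 / 0.65 / 0.50 | √(0.80/1.00) = 0.89 | 7.8–8.1% | 5.1–5.4% |
| 0.60 / 0.60 / 0.36 | √(0.96/1.28) = 0.87 | 9.2% | 5.6% |
| 0.70 / 0.70 / 0.40 | √(0.80/1.20) = 0.82 | 10.7–11.1% | 6.0–6.2% |

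**The case against.** **On efficiency.** Arm, time and arm×time is a standard model for a change endpoint. Under randomisation its estimate is unbiased and its test valid. Adjusting for baseline is therefore an improvement and does not correct an error. That stands, and the point is put as lost precision. The gap between about 67% and the stated 80% is a separate sample size question. It does not show that the model is wrong, although the change recovers much of the gap. The conditional covariate rule does not help reliably, since it depends on observed imbalance.

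**On the covariance.** A reader might infer that the week-12 standard error is wrong and that the primary test exceeds 5%. The document does not support this, for four reasons.
- It does not say that the random effect is the only covariance term. A residual structure, random slope or robust standard error is not excluded, and such detail is commonly left to the analysis plan, which is not shown. The data cleaning section also promises checks of model assumptions, although its example remedies (transformation, nonparametric analysis) do not concern covariance.
- The only correlation documented is a single 0.60. With equal correlations and variances the random-intercept standard error is right.
- The steepest pattern above, 0.70 falling to 0.40, is beyond first-order autoregressive decay (0.70² = 0.49) and is an extreme case.
- The test the protocol names is the 2-df interaction, which stays between 5.1% and 6.2% under every falling pattern tried. The larger figures belong to a 1-df week-12 contrast.

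It is also tempting to argue that selecting fatigued participants shrinks baseline variance and so makes the standard error too small. Simulation does not bear this out. With r = 0.60 throughout and baseline variance cut to 0.8 or 0.7, the week-12 contrast rejects 4.7% and 4.5% of the time.

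**Conclusion.** The efficiency point holds. It follows from the fixed effects as stated, randomisation after baseline, and the protocol's own r = 0.60: a week-12 variance 20% lower is available from data already being collected. Power rises from about 67% to 77%, and the 2-df test also gains. The 20% is for complete data, equal variances and a baseline-to-week-12 correlation of 0.60; a lower correlation makes the saving larger.

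The standard error point is secondary and conditional on two things the document does not settle: that the random effect is a plain random intercept, and that correlation falls with time. If both are true with correlations 0.65/0.65/0.50, the week-12 standard error and interval are about 11% too narrow and a 1-df test runs at about 8%. That case has a baseline-to-week-12 correlation of 0.50, where the efficiency saving is 25%, so the 11% and the 20% should not be quoted together as one scenario.

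**What to change.** 1. Use the baseline value efficiently, in one of two ways. Either keep baseline in the response, drop the arm main effect and let the arms differ only at weeks 6 and 12; or take weeks 6 and 12 as the response with baseline MFSI×visit as covariate.
2. State the tests to match. The week-12 arm difference estimates the stated objective. The counterpart of the present 2-df test is the joint test of the arm differences at weeks 6 and 12. In the covariate version, the arm×visit term alone would test only whether the effect differs between those two visits. In the common-baseline version, the coding must give both arms the same baseline cell, because a full arm×time term would restore the free means.
3. Specify an unstructured 3×3 within-participant covariance with Kenward-Roger degrees of freedom.
4. Use the same form for the rest-activity and glucose outcomes.

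The cost is analysis-plan wording and code of similar length, settled before the data are unblinded. If all three visits stay in the response, the unstructured covariance has 6 parameters against 2 for a random intercept, so 4 more. Recruitment, visits and participants are unaffected.

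### Covariates are chosen by observed baseline imbalance and added to a model whose arm×time test they barely touch, so the rule gives little of the protection it promises

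*Protocol article*

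**What the plan says.** The Data analysis section of the protocol article states the rule twice. It opens with a comparison of the arms at baseline, after which "the relevant variables (e.g., age) that differ by group will be included as confounders in hypotheses testing". Later it lists age, body mass index, psychological symptoms and time since completing treatment as examples, and says that any which "are not evenly distributed between the two groups, they will be added to the model". It gives no fixed list, no criterion for uneven distribution, and no form in which the covariates enter.

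The same section sets the primary model. MFSI score is the outcome; the fixed effects are arm, time (baseline, 6 and 12 weeks) and their interaction; participant is a random effect; the interaction is tested at 0.05. Baseline MFSI is therefore one of the outcome values and not a covariate. The Procedures section says that randomisation is unstratified.

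**The concern.** Any imbalance after proper randomisation is chance. The useful reason to adjust is that a covariate predicts the outcome, and that can be judged before the data are seen. The stated rule looks only at whether the arms differ.

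The rule also has to work inside this particular model. The tested quantity is a difference between arms in change from baseline. A covariate measured once and entered as a main effect shifts a participant's three scores by the same amount and drops out of the change. A reader of the results could believe that an imbalance in age or body mass index had been dealt with when the primary estimate had not moved.

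With no stratification in a population mixed in cancer type and treatment history, this rule is the plan's only stated response to imbalance. The mechanistic outcomes are to use similar models, so it carries over to them.

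**Working it through.** **Inputs.** From Sample size and power calculation: "80% power at the 0.05 two-sided significance level"; an effect of 0.50 baseline SD for the difference in change; "Assuming correlations [69] of 0.60 between repeated MFSI measurements"; and "The estimated attrition is approximately 20%, thus the estimated retention rate is 76 (38:38) evaluable participants". The baseline SD is set to 1 and ρ = 0.60 is applied to every pair of visits.

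**The plan's own figure.** Power = Φ(0.50 / √(2V/38) − 1.96), where V is the per-person variance of the contrast.

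- Mean of weeks 6 and 12 minus baseline: V = (1+ρ)/2 + 1 − 2ρ = 0.80 + 1 − 1.20 = 0.60. Then √(1.20/38) = 0.178, 0.50/0.178 = 2.81, power 80.3%. The stated 80% reproduces on this contrast.
- Baseline to week 12, the named endpoint: V = 2(1−ρ) = 0.80. Then √(1.60/38) = 0.205, 0.50/0.205 = 2.44, power 68.3%. This is the starting point for the gains below.

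**Step 1: what a main effect does with complete data.** Write y(i,t) = arm, time and arm×time terms + βx(i) + b(i) + e(i,t). In y(i,3) − y(i,1), both βx(i) and the participant effect b(i) cancel. The contrast between arms and its standard error then rest on within-person differences alone.

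Random-intercept fits to simulated data (38 per arm, three visits, 0.5 SD imbalance in x) agree. In one dataset the week-12 arm×time estimate was −0.51923 (SE 0.2161) both without and with x, and −0.696 (SE 0.241) with x×time. Over 60 datasets in each of two scenarios, the largest change in the estimate from adding x was below 1e-14.

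**Step 2: with dropout.** The set-up was 48 per arm, about 20% dropout depending on x and baseline score, all observed data used, and 100 datasets per scenario.

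- Adding x as a main effect moved the estimate by 0.014 to 0.020 SD on average (largest 0.056 to 0.072), against a standard error of about 0.20 to 0.21. The mean standard error fell by about 0.5%.
- Three further datasets with a 0.5 SD imbalance built in moved by 0.029, 0.006 and 0.006.
- Where x did predict change, x×time reduced the mean standard error from 0.213 to 0.204.

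**Step 3: if the covariates do act on change.** This step uses a different analysis, a regression of the 12-week change. It assumes four independent covariates, each correlated r with change (the document gives no value), 38 per arm, an effect of 0.50 SD and V = 0.80. The imbalance rule admits a covariate if the arms differ at p<0.05.

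At r = 0.25 the repeated simulations gave:

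| Strategy | Power | Type I error |
|---|---|---|
| No adjustment | about 67% | 4.9% |
| Adjust if imbalanced | 67–68% | about 4.1–4.6% |
| Always adjust | 76–78% | 4.9–5.1% |

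The always-adjust power depends on r:

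| r | None | Always adjust |
|---|---|---|
| 0 | 67–68% | about 65% |
| 0.10 | 66–67% | 65–67% |
| 0.15 | about 67% | 68–69% |
| 0.25 | about 67% | 76–78% |

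**Step 4: baseline MFSI as a covariate.** This needs only the protocol's ρ. V falls from 2(1−ρ) = 0.80 to 1−ρ² = 0.64, which is 20% lower. Then √(1.28/38) = 0.184, 0.50/0.184 = 2.72, power 77.8%.

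**The case against.** Four points can be made for the plan.

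- **The article does not say that covariates enter as main effects.** Covariate×time terms are not excluded, and a condensed article may leave the form to an analysis plan that is not shown. This stands in part. Main effects are the natural reading of adding variables to a model whose interactions are otherwise spelled out, but not the only one. Psychological symptoms are measured at every visit and would not cancel if entered as time-varying. However, the section speaks of characteristics compared before hypothesis testing, which points to baseline values. Selection by imbalance is stated outright under either reading.
- **Invariance is exact only with complete data.** This stands. The plan expects about 20% attrition and allows maximum likelihood or multiple imputation, so the estimate would move a little. The complete-case result may nevertheless be the one reported, under the missing-data rule.
- **The two faults cannot hold together.** This stands. If the covariate leaves the arm×time test unchanged, selecting it cannot make that test conservative or data-dependent. The type I error and power figures in Step 3 apply only if the covariates act on change.
- **Adjustment is not free.** This stands. With uninformative covariates, always adjusting four of them loses about 3 points of power.

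A reader might also infer that the primary test is biased or invalid. The document does not support that. In the first case the result is the unadjusted randomised comparison; in the second the type I error lies slightly below 5%.

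**Conclusion.** The rule is poorly fixed, but it does not endanger the validity of the primary analysis. As baseline main effects, the added covariates change the tested effect not at all with complete data, and on average by less than a tenth of its standard error with about 20% dropout. The promised handling of imbalance is therefore close to nominal. If coded to act on change, they are picked for the wrong reason: the rule recovers almost none of the precision that prognostic covariates offer, and the test becomes slightly conservative.

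The cancellation result assumes time-constant covariates entered as main effects with a random intercept. The conservatism figure assumes r = 0.25 for each of four covariates.

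It would be tempting to blame the imbalance rule alone for about 10 points of lost power. That is not supported. A pre-specified main effect would gain nothing for arm×time either, and the 10 points depend on an assumed correlation. The gain that follows from the protocol's own ρ is the one from baseline-MFSI adjustment, about 68% to 78%. This should be fixed, and it is cheap to fix.

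**What to change.** Keep the baseline table as description, but drop it as a way of choosing covariates. Before outcome data are seen by arm, name a short list expected to predict fatigue from those the plan already mentions (age, body mass index, time since completing treatment, baseline psychological symptoms). State the form of adjustment as one of the following:

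- keep the three-visit model and enter each covariate with its time interaction; or
- model the week-6 and week-12 scores with arm, visit and arm×visit, taking baseline MFSI and the listed covariates as covariates, and read the arm effect at week 12.

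The second also delivers the gain from baseline MFSI. Report the model without covariates as a sensitivity analysis, and apply the same wording to the mechanistic models.

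The cost is a change of wording and a few degrees of freedom with about 76 evaluable participants. No new data are needed. Because uninformative covariates lose power, the list should stay short.
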